## 20   **Study Design**

21   We present the design of a randomized, multicenter, controlled study, whose aim is to assess the  
22   effectiveness of delivery room assistance with intact placental circulation in comparison to cord  
23   milking for improving outcomes in very preterm newborns. A total of 212 infants born at 23+0 to  
24   29+6 weeks of gestational age will be enrolled and randomized to receive assistance with intact  
25   placental circulation or cord milking at birth.

26   The primary outcome of the study is the comparison between groups of the risk of developing the  
27   composite outcome of grade 3-4 intraventricular hemorrhage (3-4 IVH), bronchopulmonary  
28   dysplasia (BPD) and mortality. Secondary outcomes include the comparison between groups of  
29   the need and duration of respiratory support, hemodynamic parameters and cerebral  
30   oxygenation, need and number of blood transfusions and inotropic drugs use in the first 24 hours.

31

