### 115 **Secondary Outcomes**

116

117 Secondary outcome measurements include the following:

118 1) 3-4 grade IVH

119 2) BPD

120 3) Mortality

121 Other secondary collected data will be:

122 1) Need for mechanical ventilation in the first 24 h of life

123 2) Peak hemoglobin level and hematocrit in the first 24 h of life

124 3) Need and number of blood transfusions

125 4) Need and duration of non invasive and invasive respiratory support

126 5) Use of inotropic drugs in the first 24 hours of life,

127 6) Cerebral oxygenation in the first 24 hours,

128 7) Superior vena cava blood flow in the first 24 hours.

129

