### 130 **Further collected data**

131 The following data will be recorded for each infant: gestational age; birth weight; sex; mode of  
132 delivery; Apgar score at 1 and 5 min; main maternal pathologies; antenatal steroid treatment;  
133 maternal analgesia/anesthesia; highest FiO2 in the delivery room; need for resuscitation  
134 procedures at birth (positive pressure ventilation, intubation, chest compressions, drugs); body  
135 temperature at admission; hemoglobin and hematocrit maximum values in the first 24 hours; the  
136 highest FiO2 and mean airway pressure (MAP) values; need and duration of non-invasive  
137 (NCPAP, biphasic positive airway pressure, nasal intermittent mandatory ventilation), and  
138 invasive (patient-triggered ventilation or high frequency oscillatory ventilation) respiratory support;  
139 and need and duration of nitric oxide therapy. We will also report the occurrence of patent ductus  
140 arteriosus (PDA) requiring pharmacological or surgical treatment, of IVH, periventricular  
141 leukomalacia (PVL), NEC, ROP, and hospital stay duration.

142 A diagnosis of sepsis will be based on clinical and laboratory data (white cell count, C-reactive  
143 protein concentration) and will be confirmed by positive blood cultures (9). IVH will be graded  
144 according to a standard classification system (10). A diagnosis of PVL will be made when cystic  
145 areas are detected by cerebral ultrasonography at 40 weeks post-conception birth (11). BDP will  
146 be diagnosed according to the definition by Jobe and Bancalari (12). ROP will be graded  
147 according to the international classification of retinopathy of prematurity (13). NEC will be  
148 diagnosed in agreement with classical Bell's criteria (14).

149

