209 minutes (17) and 85% by 10 minutes of life (18) with a heart rate  $>100$  bpm, despite nasal CPAP  
210 at 5-8  $\text{cmH}_2\text{O}$ .

211 A pulse oximeter (Radical-7, Masimo Corporation, USA) is positioned on Lifestart trolley, and the  
212 trolley, together with all devices placed on it, is covered with a transparent sterile coverage in case  
213 of cesarean section. Thus, the obstetrician hands place the newborn on a completely sterile trolley  
214 and then come back to the mother abdomen, at that moment the neonatologist begin to assist the  
215 baby (with aspiration if necessary, positioning pulse oximeter probe, starting nCPAP/PPV as  
216 necessary). Heart rate will be assessed by auscultation and pulse oximeter. For babies assisted  
217 with an intact cord on Lifestart trolley two person provide bedside neonatal assistance (1 doctor  
218 and 1 nurse). During the 3-minutes period of delayed cord clamping the prevalent procedure will be  
219 to assist respiratory function with nCPAP/PPV till intubation if necessary. If necessary, an early  
220 surfactant administration will be performed in delivery room, but not during the 3-minutes period of  
221 delayed cord clamping.

222 Daily clinical care of the enrolled patients will be performed by the attending physicians in  
223 accordance with the common practice at each center. Daily fluid intake will be started at 80-90  
224 ml/kg and gradually increased by 10–20 ml/kg/day based on changes in body weight, serum  
225 sodium concentrations, and osmolality, with a target intake of 150–160 ml/kg at the end of the  
226 first week of life. In case of hypotension refractory to the fluid-replacement therapy, dopamine

227 and/or dobutamine treatment will be provided. For the treatment of respiratory distress syndrome  
228 (RDS), infants will receive oxygen therapy, respiratory support, and rescue surfactant treatment  
229 to achieve the following therapeutic targets: PaO2 50–60 mmHg, PaCO2 < 65 mmHg, pH > 7.20,  
230 and SpO2 90–95 %. To maintain an adequate SpO2, infants with an FiO2 ≥0.30 will be treated  
231 with surfactant (200 mg/kg Curosurf, Chiesi Pharmaceuticals, Parma, Italy) through the  
232 intubation-surfactant-extubation (INSURE) procedure or less invasive surfactant administration  
233 (LISA) strategy. All infants who will need MV will be treated with surfactant and will then be  

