#### 4.1.2 Secondary efficacy variables

The secondary efficacy variables are:

- The single components of the composite endpoint
- The variables reported in list below:
  - 1 min Apgar score
  - 5 mins Apgar score
  - FiO2 max in delivery room
  - Use of neopuff
  - Use of physiological solution
  - Use of sodium bicarbonate
  - Body temperature (°C) at intensive care admission
  - Surgical treatment for patent ductus arteriosus (PDA)
  - Incidence of IVH
  - Use of non-invasive mechanical ventilation
  - Duration of non-invasive mechanical ventilation (days)
  - Use of invasive mechanical ventilation
  - Duration of invasive mechanical ventilation (days)
  - iNO administration
  - Duration of iNO administration (days)
  - Need of erythrocyte concentrate transfusions
  - Number of erythrocytes concentrate transfusions
  - Use of oxygen therapy
  - Duration of oxygen therapy (days)
  - FiO2 max during oxygen therapy (%)
  - Dopamine use in the first 24 hours
  - Dobutamine use in the first 24 hours
  - Overall duration of hospitalization (days)
  - 3-hour cerebral oxygenation
  - 6-hour cerebral oxygenation
  - 12-hour cerebral oxygenation
  - 18-hour cerebral oxygenation
  - 24-hour cerebral oxygenation
  - Superior vena cava blood flow in the first 24 hours (ml/Kg/min)
  - PAP value (mmHg)
  - Right ventricular ejection (ml/Kg/min)
  - Left ventricular ejection (ml/Kg/min)
  - Presence of transductal shunt
  - Hb max (g/dl) in the first 24 hours
  - Ht max (%) in the first 24 hours
  - 3-hour average PAS (mmHg)
  - 6-hour average PAS (mmHg)
  - 12-hour average PAS (mmHg)
  - 18-hour average PAS (mmHg)
  - 24-hour average PAS (mmHg)

S/D AMS  
PI AMS  
RI AMS  
AMS diastolic flow  
S/D ACA  
PI ACA  
RI ACA  
ACA diastolic flow

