## 4.2 SAFETY VARIABLES

Safety of the study interventional procedures will be evaluated by the following variables:

Intubation in delivery room  
Compressions in delivery room  
Use of i.v. adrenaline in delivery room  
Use of ET adrenaline in delivery room  
Use of surfactant in delivery room  
Total number of surfactant doses  
CRIB II score  
Max serum bilirubin  
Exchange transfusions  
Need of mechanical ventilation in the first 24 hours  
Duration of mechanical ventilation in the first 24 hours (hrs)  
Pharmacological closure of PDA  
Incidence of NEC  
Incidence of PLV  
Incidence of IVH  
Incidence of ROP  
Incidence of sepsis

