| Total          |               |   |       |   |       |   |

NOTE: Arm A = UMBELICAL CORD MILKING, Arm B = DELAYED UMBELICAL CORD CLAMPING

TABLE 5.20: DURATION OF OXYGEN THERAPY BY TREATMENT ARM (5)

*INTENTION-TO-TREAT POPULATION*

|                 |                | Treatment Arm |       | Total |
|-----------------|----------------|---------------|-------|-------|
|                 |                | Arm A         | Arm B |       |
| Duration (days) | N              |               |       |       |
|                 | Missing        |               |       |       |
|                 | Mean           |               |       |       |
|                 | SD             |               |       |       |
|                 | Median         |               |       |       |
|                 | Minimum        |               |       |       |
|                 | First quartile |               |       |       |
|                 | Third quartile |               |       |       |
|                 | Maximum        |               |       |       |

NOTE: Arm A = UMBELICAL CORD MILKING, Arm B = DELAYED UMBELICAL CORD CLAMPING

TABLE 5.21: FiO2 MAX DURING OXYGEN THERAPY BY TREATMENT ARM (5)

*INTENTION-TO-TREAT POPULATION*

|              |                | Treatment Arm |       | Total |
|--------------|----------------|---------------|-------|-------|
|              |                | Arm A         | Arm B |       |
| FiO2 max (%) | N              |               |       |       |
|              | Missing        |               |       |       |
|              | Mean           |               |       |       |
|              | SD             |               |       |       |
|              | Median         |               |       |       |
|              | Minimum        |               |       |       |
|              | First quartile |               |       |       |
|              | Third quartile |               |       |       |
|              | Maximum        |               |       |       |

NOTE: Arm A = UMBELICAL CORD MILKING, Arm B = DELAYED UMBELICAL CORD CLAMPING

TABLE 5.22: DISTRIBUTION OF PATIENTS BY DOPAMINE USE IN THE FIRST 24 HOURS AND TREATMENT ARM (1)  
*INTENTION-TO-TREAT POPULATION*

|               | Treatment Arm |   |       |   | Total |   |
|---------------|---------------|---|-------|---|-------|---|
|               | Arm A         |   | Arm B |   |       |   |
|               | N             | % | N     | % | N     | % |

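### The protocol lists inotrope use in the first 24 hours as one outcome, but the SAP tests dopamine and dobutamine separately and has no combined analysis

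*Combined protocol and SAP*

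**What the plan says.** **Inotropes.** The protocol's Secondary Outcomes section lists "Use of inotropic drugs in the first 24 hours of life" as one item and names no drug. The Study Design part of the abstract repeats it among the secondary outcomes: "need and number of blood transfusions and inotropic drugs use in the first 24 hours". Under Study Procedures, for hypotension that does not respond to fluid replacement, dopamine "and/or dobutamine treatment will be provided", so either drug or both may be given.

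SAP 4.1.2 has two variables instead: "Dopamine use in the first 24 hours" and "Dobutamine use in the first 24 hours". Appendix 1 gives each its own ITT yes/no table with a chi-square or Fisher test. Table 5.22 is titled "DISTRIBUTION OF PATIENTS BY DOPAMINE USE IN THE FIRST 24 HOURS AND TREATMENT ARM (1"), and Table 5.23 is its dobutamine twin. SAP 5.2.3 applies no multiplicity adjustment to the secondary variables.

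**PDA.** The protocol's Further collected data section treats patent ductus "arteriosus (PDA) requiring pharmacological or surgical treatment" as one item. The SAP lists surgical treatment as a secondary efficacy variable (4.1.2; Table 5.9, ITT) and "Pharmacological closure of PDA" as a safety variable (4.2; Table 6.12, safety population).

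**The concern.** The protocol item is most naturally read as asking whether an infant was given any inotrope. SAP 2.2 frames the hypothesis in the same way, as less use of vasoactive drugs taken together. The planned output answers two narrower questions. Because an infant may have had both drugs, the two tables cannot be added to give the protocol's outcome.

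If the two drug tests disagree, nothing pre-stated says which one answers the protocol's question. Choosing the definition after seeing the results would then be a post hoc decision on a pre-specified outcome. Each single-drug outcome may also have fewer events than the combined one, and so less power.

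For PDA, a reader who wants the proportion treated by either route would have to combine two tables that need not contain the same infants.

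**Working it through.** **1. Text check.** Neither SAP 4.1.2 nor Appendix 1 contains an any-inotrope variable or a dopamine-by-dobutamine cross-table. The SAP states no figure for this outcome, so there is none to reproduce.

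**2. What the two tables can reveal.** With single-drug proportions *a* and *b* in one arm, max(*a*, *b*) ≤ P(any) ≤ *a* + *b*.

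Assumed example: control 20% dopamine and 10% dobutamine; experimental 12% and 6%.
- Control, any inotrope: between 20% and 20 + 10 = 30%.
- Experimental, any inotrope: between 12% and 12 + 6 = 18%.
- Overlap may differ by arm, so the difference could be anything from 20 − 18 = 2 points to 30 − 12 = 18 points.

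The same two tables are compatible with almost no difference and with a large one.

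**3. Power under assumed rates.** The documents give no inotrope rates. I use *n* = 100 per arm (SAP 2.7), two-sided α = 0.05 and the normal approximation to the chi-square test:

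power = Φ[(|p₁ − p₂| − 1.96·SE₀) / SE₁], where SE₀ = √(2p̄(1 − p̄)/n) and SE₁ = √(p₁(1 − p₁)/n + p₂(1 − p₂)/n).

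For any inotrope at 30% vs 15%: p̄ = 0.225, SE₀ = 0.0591, SE₁ = 0.0581. Then (0.15 − 0.1158)/0.0581 = 0.59, giving 72%.

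The single-drug test when any use is 30% vs 15%:

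| Assumption | Single-drug rates | Power |
|---|---|---|
| Even split, no overlap | 15% vs 7.5% | 39% |
| Drug given to 80% of treated infants | 24% vs 12% | 60% |
| Drug given to 90% of treated infants | 27% vs 13.5% | 66% |
| Full overlap | 30% vs 15% | 72% |

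At a lower base rate (20% vs 10% any use) the combined test has 51%, against 27% per drug with an even split and no overlap (10% vs 5%).

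**4. Two tests for one question.** Two unadjusted tests at 0.05 have a joint false-positive chance of 1 − 0.95² = 9.75% if independent.

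**5. PDA populations.** Under Study Procedures, an infant whose assigned procedure is not performed receives immediate clamping, which is neither study procedure. SAP 3.4 and 3.5 keep that infant in the efficacy analyses as randomised and exclude it from the safety analyses. An infant given the other arm's procedure changes group for safety. Tables 5.9 and 6.12 can therefore differ in both denominator and grouping. SAP 5.2.3 and 5.2.4 also report both variables on the per-protocol population, but still as separate items.

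**The case against.** The strongest reply is that inotrope use is analysed. Both inotropes that the protocol names are secondary efficacy variables, tested by arm on ITT. A reader might infer that the outcome is ignored altogether, but the documents do not support that: only the combined outcome is missing. The protocol also speaks of use, where neighbouring items speak of need, and places the item under other secondary data, below the three named component outcomes. A drug-by-drug reading is thus possible, though less natural, and the abstract does call inotrope use a secondary outcome.

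A reader might quote 72% against 39% as the cost. That contrast needs an exactly even split with no overlap. A dominant drug or substantial overlap shrinks the loss, to nothing at full overlap.

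A reader might also say that the choice of drug reflects centre habit. The protocol says only that daily care follows each centre's common practice; it does not describe how the drug is chosen. That remains conjecture.

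On PDA, three limits stand. Treated PDA is further collected data, not a listed secondary outcome. Its parts are not split as the inotropes are, because both inotrope variables stay on ITT. Nor would a shift from surgery to drug closure be hidden, since Table 6.12 shows drug closure by arm, and both parts share the per-protocol population.

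The unadjusted-testing worry applies to the whole secondary list and does not single out this item. None of this supplies the missing either-drug result.

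**Conclusion.** The mismatch between protocol and SAP holds. The combined inotrope outcome has no planned test, and its rate cannot be recovered from the planned tables; it can only be bounded. This rests on the text alone.

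The power effect is illustrative. At an assumed 30% vs 15% with 100 per arm, it runs from no loss (full overlap) to a fall from 72% to 39% (even split, no overlap). Without rates or overlap data, no single figure within that range can be preferred.

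The PDA point is real but lesser: one item that the protocol collects is reported in two parts, on ITT as randomised and on the safety population as treated. Both points concern secondary reporting only; the primary analysis is unaffected.

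**What to change.** In SAP 4.1.2 and beside Tables 5.22–5.23, add *Any inotropic drug (dopamine or dobutamine), first 24 hours* on ITT as the tested outcome. Keep the two single-drug tables as description, without tests. State the derivation: yes if either drug is yes, no if both are no, otherwise missing. The protocol does not define inotropic drugs, so the SAP should also say whether the delivery-room adrenaline variables in 4.2 are outside this definition.

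As the lesser change, add one ITT row for PDA treated by drug or surgery, with the two routes listed below it.

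The cost is SAP wording and two derived variables built from items already tabulated; no new data are needed. The small downside is a late change, since SAP 2.4 reports enrolment as completed. Date and document it before results by arm are seen; if they have been seen, label the new rows post hoc.

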## 4.2 SAFETY VARIABLES

Safety of the study interventional procedures will be evaluated by the following variables:

Intubation in delivery room  
Compressions in delivery room  
Use of i.v. adrenaline in delivery room  
Use of ET adrenaline in delivery room  
Use of surfactant in delivery room  
Total number of surfactant doses  
CRIB II score  
Max serum bilirubin  
Exchange transfusions  
Need of mechanical ventilation in the first 24 hours  
Duration of mechanical ventilation in the first 24 hours (hrs)  
Pharmacological closure of PDA  
Incidence of NEC  
Incidence of PLV  
Incidence of IVH  
Incidence of ROP  
Incidence of sepsis

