## 282 **Data Safety and Monitoring Board**

283 Safety and tolerability will be assessed by monitoring the frequency and severity of adverse  
284 events. Safety end-points will include incidence, severity and causality of reported serious  
285 adverse events (SAEs), namely changes in occurrence of the expected common prematurity  
286 complications and routine clinical laboratory test assessments, and the development of  
287 unexpected SAEs in this high risk population. All SAEs will be followed until satisfactory  
288 resolution or until the investigator responsible for the care of the participant deems the event to  
289 be chronic or the patient to be stable. All expected and unexpected SAEs will be reviewed by the  
290 local principal investigators to determine if there is a reasonable suspected causal relationship  
291 with the intervention. A monitoring board including an independent assessor (not involved in the  
292 study) from the IRCCS San Martino Hospital (Genova, Italy) and assessors from each  
293 participating hospital will review all the deaths and adverse effects. If there is a reasonable  
294 suspected causal relationship with the intervention, SAEs will be reported to the Ethics  
295 Committee to guarantee the safety of the participants.  
296 An interim analysis will be performed on the primary endpoint and SAEs from the first 100 infants  
297 enrolled. The interim analysis will be performed by the statistician, blinded for the treatment  
298 allocation, who will report to the principal investigator. The principal investigator will discuss the  
299 results of the interim analysis with the monitoring board and the trial will be ended in case of

300 harm. Criteria for stopping for harm include: 1) a statistically significant difference in SAEs  
301 between the treatment groups, and 2) a reasonable suspected causal relationship between the  
302 intervention and SAEs, and 3) a significant increase in occurrence of SAEs in respect to the  
303 incidence reported in newborns of same gestational age in Vermont Oxford Database.

304

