### 2.3.2 Secondary objectives

- To compare in the two groups of preterm infants in which assistance with intact placental circulation or assistance after cord milking has been given the proportion of subjects experiencing at 36 weeks of post-conceptual age each of the events included in the composite outcome.
- To assess the presence of interaction between type of assistance and gestational age, and between type of assistance and type of delivery, on the primary composite endpoint and on each of its components.
- To compare in the two groups of preterm infants in which assistance with intact placental circulation or assistance after cord milking has been given the results related to the identified secondary efficacy endpoints.
- To evaluate the safety of the two assistance strategies.

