### 3.4 SAFETY POPULATION

The safety population will include all randomized preterm infants who have received assistance according to one of the two interventional protocol procedures. Patients will be analysed according to type of assistance they received.

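### The protocol makes the incidence, severity and causality of serious adverse events its safety endpoints; the SAP's safety analysis covers some named complications but omits overall SAE incidence, relatedness, unexpected SAEs and most severity.

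*Combined protocol and SAP*

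**What the plan says.** **Protocol, Data Safety and Monitoring Board.** The endpoint sentence begins "Safety end-points will include incidence, severity and causality of reported serious" and continues "adverse events (SAEs), namely changes in occurrence of the expected common prematurity" "complications and routine clinical laboratory test assessments, and the development of" unexpected SAEs in this high-risk population. On causality: "All expected and unexpected SAEs will be reviewed by the" local principal investigators, who judge whether a link with the intervention is reasonably suspected. SAEs also enter the monitoring plan: "An interim analysis will be performed on the primary endpoint and SAEs from the first 100 infants". A significant difference in SAEs between the arms is one of the criteria for stopping for harm.

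**SAP.** Section 2.3.2 sets the objective "To evaluate the safety of the two assistance strategies". Section 4.2 opens with "Safety of the study interventional procedures will be evaluated by the following variables" and gives 17 items. Section 5.2.4 analyses the safety parameters with the methods used for the other secondary variables, in the safety and per-protocol populations. Section 6 of Appendix 1 has one table per listed item, Tables 6.1 to 6.17. The term SAE occurs in the SAP only in its list of abbreviations.

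**Who is counted.** SAP 3.4 limits the safety population to randomised infants "who have received assistance according to one of the two interventional protocol procedures", grouped by what they received. SAP 3.5 removes infants assisted with an off-protocol procedure from the safety analyses. They are also outside the per-protocol population.

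**The concern.** The two documents answer the safety question with different sets of variables. The protocol's set is open: any serious event, graded, judged for causality and classed as expected or unexpected. The SAP's set is closed: named complications, interventions and measurements. A closed list cannot show an event that nobody thought to list, and the protocol asks specifically for such events. The investigators' causality judgements have no place in the planned analysis either.

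If the SAP were followed as written, the report could conclude on the safety of the two strategies without showing, by arm, how many infants had an SAE, how many had one judged related, or how many had an unexpected one. The open-label design adds to the need for a complete count in both arms, since a reader cannot fall back on blinding.

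**Working it through.** No figure in the plan has to be reproduced. The check sets the protocol's declared elements against SAP 4.2, SAP 5.2.4 and Tables 6.1 to 6.17.

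**Step 1: sort the SAP's 17 safety variables.**
- Common prematurity complications: NEC, PVL (PLV in the SAP), IVH, ROP, sepsis, pharmacological closure of PDA = 6.
- Laboratory measure: maximum serum bilirubin = 1.
- Interventions, support or illness score: delivery-room intubation, compressions, i.v. adrenaline, ET adrenaline and surfactant (5); number of surfactant doses, CRIB II, exchange transfusion, need for and duration of ventilation in the first 24 hours (5) = 10.
- Total: 6 + 1 + 10 = 17. Variables that count SAEs, related SAEs or unexpected SAEs: 0.

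**Step 2: compare element by element.**

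| Protocol element | In the SAP's safety analysis | Missing |
|---|---|---|
| Incidence of SAEs | Six named complications, each separately | Infants with at least one SAE |
| Expected complications | Those six; death appears under efficacy (Tables 4.11 to 4.15, ITT) | Any serious complication not named |
| Laboratory assessments | Maximum bilirubin | Any other laboratory finding |
| Severity | IVH grades 1 to 4 (Table 6.15) | Severity of everything else: NEC, PVL and ROP are yes/no, and sepsis is split by time of onset only |
| Causality | None | All of it |
| Unexpected SAEs | None | All of it |

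**Step 3: look for an explanation.** The SAP comments on other matters where it and the protocol differ. Section 2.5.2 explains why the short-cord criterion was removed, and section 3 notes that analysis populations had not been identified in the protocol. On the SAE endpoints it is silent.

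**Step 4: trace the infants who received neither procedure.** Under the protocol's Study Procedures, an infant in either group whose assigned procedure is not performed receives immediate clamping. SAP Table 1.6 has a row for treatment received other than arm A or arm B. If immediate clamping counts as off-protocol, which the SAP does not say, SAP 3.5 takes these infants out of all 17 safety tables. They stay in the ITT tables, so their deaths, severe IVH and BPD are still seen. Their NEC, PVL, ROP and sepsis would not be.

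**The case against.** The strongest case on the other side has five parts.

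1. **The protocol itself explains what it means by SAEs.** The endpoint sentence goes on to describe them as changes in expected prematurity complications and laboratory assessments, as well as unexpected events. The SAP tabulates a good part of the first two. This stands. A reader might infer that the SAP contains none of the protocol's safety endpoints, and the documents do not support that.
2. **Death is compared by arm.** Tables 4.11 to 4.15 do so on all randomised infants. This also stands: death is filed under efficacy, not lost.
3. **Appendix 1 is not an exhaustive list of output.** SAP 5.2 says the per-protocol tables are left out of it, and SAP 3.6 promises a list of deviations that has no table shell. So the absence of an SAE table does not prove that SAEs will never be reported. It does show that no by-arm SAE analysis is specified, since 4.2 and 5.2.4 do not provide one either.
4. **Monitoring continues.** Causality review, board review of deaths and adverse effects, and reporting to the Ethics Committee are protocol processes that the SAP does not cancel. They protect infants during the trial but do not supply the final comparison between arms.
5. **The versions may differ.** The SAP is based on protocol version 4.0. It describes the interim analysis as a feasibility check that involved no efficacy variable, whereas the protocol text has it on the primary endpoint and SAEs. The protocol text available may not be the one from which the SAP was written. This lowers certainty, but the two documents as they stand still conflict.

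**Conclusion.** The concern holds in a limited form. The SAP's safety analysis covers part of the declared endpoints (six named complications, one laboratory measure and IVH grade), and death is compared elsewhere. It omits overall SAE incidence, relatedness, unexpected SAEs and severity other than IVH grade, without giving a reason. The size is a count: 0 of 17 planned safety variables and tables report any of the first three, and 1 grades severity. No precision can be attached to a comparison of SAEs, because the documents give no SAE rate.

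This is a conflict between two documents on a declared endpoint, not merely missing detail. It does not touch the primary analysis, and it does not show that monitoring failed or that SAEs went unrecorded. The conclusion assumes that the protocol's endpoint sentence was in force when the SAP was written. The point about off-protocol infants further assumes that immediate clamping counts as an off-protocol procedure.

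**What to change.** Add to SAP 4.2, SAP 5.2.4 and Appendix 1, by arm:
- the number and percentage of infants with at least one SAE, with at least one SAE judged related, and with at least one unexpected SAE;
- SAE severity, where it was recorded;
- the risk difference with its 95% CI for any SAE and for any related SAE.

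Present these by assigned arm on all randomised infants, alongside the as-treated safety population. The first view counts infants who received an off-protocol procedure, and the second keeps the SAP's existing approach. State in SAP 3.5 whether immediate clamping is off-protocol. If the sponsor does intend the 17 listed variables to replace the SAE endpoints, the SAP should say so and give the reason.

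The cost is two or three tables. The protocol already requires SAEs to be reported and reviewed for causality, so no new follow-up of infants should be needed. However, neither document describes an SAE form, a severity scale or a list of expected events. If the reports and causality reviews are not already coded in the eCRF, they will have to be extracted.
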